### Ethics

Ethical approval for the study was granted by the Cambridgeshire 2 Research Ethics Committee, Addenbrooke’s Hospital Cambridge, UK (REC reference: 09/H0308/168).

### Assessments and outcome measures

#### *Self-report battery*

**Edinburgh handedness inventory** The Edinburgh Handedness Inventory [33] assesses preferred hand use across different tasks and generates a single score ranging from -100 to +100 (i.e., the laterality quotient) indicative of overall handedness laterality. Across a series of tasks, participants are requested to indicate which hand typically performs said task. In the event that neither hand is the preferred hand, a score is evenly allocated to both left and right hands. The measure is valid for use across cultures and between sexes.

**Spielberger state-trait anxiety inventory** The Spielberger State-Trait Anxiety Inventory (STAI) [34] is comprised of two 20-item questionnaires that assess both temporary fluctuations in, and long-standing experience of anxiety symptoms. When completing the STAI-State (STAI-S), participants are asked to indicate whether each statement within a list of statements applies to them 'not at all’, 'somewhat so’, 'moderately so’, or 'very much so’ at that particular moment in time. Scores indicative of a high internal consistency are more valid than test-retest correlations when assessing the validity of transitory measures such as the STAI-S. The median alpha coefficient for the STAI-S was approximately 0.93, while the median test-retest correlation was 0.330 [34]. When completing the STAI-Trait (STAI-T), participants are asked to indicate how much each statement within a list of statements applies to them in general (almost never; sometimes; often; or almost always). The median alpha coefficient was 0.90 for the STAI-T scale indicating a high level of internal consistency, with test-retest correlations observed to be reasonably high across high school students, achieving a median-level of 0.695 [34].

The STAI-S anxiety questionnaire attempts to measure current (i.e., temporary) feelings of tension, apprehension, worry and nervousness whereas the STAI-T anxiety questionnaire attempts to measure long-standing individual differences in anxiety susceptibility. State anxiety scores can therefore be considered as reflecting the intensity of anxious feelings and trait anxiety scores can be considered as reflecting the frequency with which feelings of anxiety are experienced. Scores obtained from the STAI-S and STAI-T correlate positively with each other, particularly in the case of sequential administration.

**Bond-lader visual analogue scales** The Bond-Lader Visual Analogue Scales (VAS) is a highly sensitive questionnaire comprised of several rating scales that can detect subtle mood changes in a large sample of healthy individuals aged 16–64 years [35]; c.f. [38]. The VAS measures subjective feelings relative to 16 opposing emotive word-pairs. Emotive word-pairs are presented with one word appearing at each polar end of a single line measuring 100 mm. Participants are asked to indicate how they currently feel relative to the sixteen emotive dimensions by drawing a perpendicular line on each rating line. The length from the end of the line to the participant’s mark is then measured to provide an overall score for each of the 16 scales.

While items within the VAS were once thought to assess mental alertness, physical alertness, calmness, and other feelings [38], factor analysis of the measure in healthy individuals has since revealed only three underlying scales: alertness; contentedness; and calmness [35].

**Short mood and feelings questionnaire** The Short Mood and Feelings Questionnaire (SMFQ) [36] is a 13-item self-report questionnaire that measures the presence and severity of depressive symptoms occurring in an individual over a two-week period. The scale derives from the 33-item MFQ, with each item consisting of a single statement (e.g., 'I didn’t enjoy anything at all’) rated by the respondent as 'always true’ , 'mostly true’ , 'sometimes true’ , or 'never true’.

The SMFQ reviews the core set of depressive symptoms and has been shown to discriminate child psychiatric patients from pediatric controls, and depressed from non-depressed participants in a general population sample. The SMFQ correlates highly with more extensive evaluations, like the Children’s Depression Inventory (CDI) or the Diagnostic Interview Schedule for Children (DISC), and has a robust single factor structure from ages 6 to 16 years.

### MRI assessment battery

#### *Structural MRI datasets*

A three-dimensional structural MRI (sMRI) will first be obtained for all participants to exclude for brain abnormality. MR images will be acquired on a 3.0 Tesla Magnetom Trio Tim scanner (Siemens, Surrey, England) at the Wolfson Brain Imaging Centre, University of Cambridge, UK. High-resolution dual echo sequences will be acquired in the axial plane using proton density T2-weighted sequences (Axial PD-T2; 27 slices of 4.0 mm thickness, first echo time (TE) = 12.0 ms, second TE = 104.0 ms, repetition time (TR) = 4.60s, flip angle = 150˚, field of view = 224 × 134 mm^2^, voxel size = 0.7 × 0.7 × 4.0 mm^3^, series = interleaved). High-resolution T1-weighted sequences will be acquired in the sagittal plane using a three-dimensional magnetically prepared rapid acquisition gradient echo sequence (3D-MPRAGE; 176 slices of 1.0 mm thickness, TE = 2.98 ms, TR = 2.30s, inversion time = 900 ms, flip angle = 9˚, field of view = 240 × 256 mm^2^, voxel size = 1.0 × 1.0 × 1.0 mm^3^, series = interleaved). All images will be examined and approved for inclusion by a Consultant Radiologist specialising in neuroanatomy. Grey and white matter maps will be generated for each baseline scan.

#### *Diffusion tensor imaging (DTI)*

Whole brain data will be acquired and analysed for derivation of fractional anisotropy measures of white matter integrity and tractography of selected axonal tracts mediating connections between limbic and frontal regions of interest. Thirteen diffusion-weighted directed volumes and 5 volumes without diffusion-weighting (b = 0) will be acquired (63 slices of 2.0 mm thickness, TE = 98 ms, TR = 8.30s, field of view = 192 × 126 mm^2^, voxel size = 2.0 × 2.0 × 2.0 mm^3^, series = interleaved).

#### *Functional MRI (fMRI) datasets*

Echo-planar images (EPI) depicting blood oxygen level-dependent (BOLD) contrast at a sampling time of 2.0 seconds will be acquired during the performance of three tasks and during rest. MR images will be acquired on a 3.0 Tesla Magnetom Trio Tim scanner (Siemens, Surrey, England) at the Wolfson Brain Imaging Centre, University of Cambridge, UK. Radio frequency pulses will be transmitted and received via a quadrature birdcage headcoil. To maximise magnetic field homogeneity, an automatic shim will be applied prior to functional data acquisition. MR data covering the whole brain will be acquired using echo planar T2* weighted imaging. For each functional task, 32 slices of data 3.0 mm in thickness parallel to the anterior-posterior commissure will comprise each volume of data collected (TE = 30 ms, TR = 2 s, flip angle = 78˚, and interleaved series). The field of view and voxel size will be 192 × 120 mm^2^ and 3.0 × 3.0 × 3.0 mm^3^, respectively.

**Implicit facial expression recognition task** Facial expressions taken from the Facial Expressions of Emotion: Stimuli and Tests (FEEST) [39] representing medium and high intensity morphs of sadness and happiness are presented together with neutral faces and crosshair fixations which will serve as a low-level baseline to control for possible differences in activation of low-level visual areas. Facial expressions from four male and four female actors will be selected from the stimulus set based upon similarities in Facial Action Coding System unit score and high recognition ratings for happy, sad and neutral expressions. A total of 96 trials will be presented (16 from each category) with all stimuli presented in random order in an event-related design. A jittered stimulus presentation will be used with a mean inter-trial interval (ITI) of 3.0 seconds and a range of 1.0 to 6.0 seconds following a Poisson distribution. Each stimulus will appear on the screen for 2 seconds and for each facial trial adolescents will be asked to indicate the gender of the face by depressing one of two keys on a button box. All stimuli will be presented using Visual Basic software (Microsoft), with the order of stimulus presentation pseudo-randomized across participants to minimize habituation effects.

After each scan session participants will be asked to use a 9-point Likert scale, with 1 and 9 representing low and high intensities, respectively, to indicate how happy and how sad each of the emotional faces appear.

**fMRI data acquisition–implicit facial expression recognition** The scan length is approximately 8.5 minutes, during which 249 volumes of fMRI data will be collected.

**Emotional go/no-go task** Happy, sad and neutral words will be individually presented in a blocked paradigm design. The words presented are originally reported in Murphy et al. [40], with no word overlapping with the words used in the encoding and retrieval task described below. Within each block of presented words participants will be instructed to respond by button-press to words of a chosen target category (go), while withholding responses (no-go) to distracters selected from a different category. The task design will be similar to that reported in Elliott et al. [41], with each word block lasting 24 seconds in length and consisting of 10 targets and 10 distractor words. A total of 21 word blocks will be presented where six blocks of target sad words will be presented in the context of happy (3 blocks) and neutral (3 blocks) distractor words, six blocks of happy target words will be presented in the context of sad (3 blocks) and neutral (3 blocks) distractor words, and six blocks of neutral target words will be presented in the context of happy (3 blocks) and sad (3 blocks) distractor words. Three baseline word blocks consisting of italicised words (orthographic targets) presented in the context of plain text distracter words will also be presented. A 12 second rest block during which a crosshair fixation will appear for the first 8 seconds and simple task instructions (e.g., “Press for Sad words. Ignore Happy words.”) will appear for the remaining 4 seconds prior to each word block. Within every block, each word will be presented for 450 ms and will be followed by a gray screen ITI of 750 ms.

**fMRI data acquisition–emotional go/no-go task** The scan length is approximately 13.5 minutes, during which 399 volumes of data will be collected.

**Encoding and retrieval task** Anderson’s list of 555 personality trait words rated for likeableness [42] will be used to construct a list of 90 unambiguously positive and 90 unambiguously negative words. Participants will first be asked to perform an explicit categorisation (memory encoding) task and then an unanticipated incidental memory (retrieval) task. During the encoding task, 60 personality trait words, half of which are unambiguously positive, will be presented each for 500 ms and participants will be requested to indicate whether the word is likeable or dislikeable in the context of this word being used to describe them. Each word will be preceded by a black fixation cross centrally presented against a solid gray background for 500 ms. Words will be followed by a jittered ITI following a Poisson distribution ranging from 1 to 6 seconds (mean of 3 seconds) where a centrally-presented black fixation cross will appear against a solid gray background. For the memory retrieval task, 120 personality trait words will be presented, of which half will be repeated from the categorisation task and half will be new words (distractors) comprised of an equal number of unambiguously positive and unambiguously negative distractor words. Participants will be asked to indicate whether a presented word is new (not seen before) or old (seen before).

**fMRI data acquisition–encoding and retrieval task** The scan length is approximately 13 minutes, during which 384 volumes of fMRI data will be collected.

**Resting state** Participants will be asked to lie at rest with their eyes closed and try not to fall asleep during continuous fMRI data acquisition.

**fMRI data acquisition–resting state** The scan length is approximately 9 minutes, during which 265 volumes of fMRI data will be collected. To measure the magnetic field prior to and following resting state data acquisition field maps with two echo times (TE1 = 5.19 ms, TE2 = 7.65 ms) will also be acquired with the positioning of the participant kept consistent across the three scan sequences. Magnitude images for both echoes and estimated field maps will be obtained.

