### Screening and MRI assessment

At the MRI assessment adolescents and their parents will be asked to review the study information sheet one final time prior to signing the MR-IMPACT study assent and consent forms. Adolescents will be re-screened for presence of MRI contraindication, as will any adults requested to accompany adolescents in the scanner suite. Adolescents will then be asked to complete the Edinburgh Handedness Inventory [33] and the Spielberger Trait Anxiety Inventory [34]. In preparation for the tasks the adolescent will be asked to complete in the MRI scanner, three similar tasks brief in length will be practiced on a computer in advance of the actual scan. The practice tasks will be administered in the same order as the MRI tasks are presented to minimise confusion. Patients will then be asked to complete the Spielberger State Anxiety Inventory [34] before attending the 1.5 hour MRI session. Upon completion of the MRI session, patients will be asked to complete the Bond-Lader Visual Analogue Scales [35] and then the Mood and Feelings Questionnaire-Short version [36]. Lastly, patients will be asked to complete two computerised tasks in follow-up to one of the completed fMRI tasks.

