### Follow-up assessment

Patients who were randomized to the CBT arm of the IMPACT clinical trial who have completed a minimum of 6 out of a maximum of 20 offered CBT therapy sessions will be invited back for a second MRI visit approximately 24 weeks following their first therapy appointment. All healthy comparison participants will be invited back for a second MRI visit at least 24 weeks from their first scan date to ensure a comparable length of time has passed between scans across groups. Due to financial constraints, no sMRI and DTI sequences will be performed at the second MRI visit. All participants will complete the same fMRI tasks collected during the first MRI visit (e.g., implicit facial expression recognition, emotional go/no go, encoding and retrieval, and resting state tasks). In line with procedures undertaken at the first scan, STAI measures will be obtained prior to scanning whereas SMFQ and Bond VAS measures will be obtained after the scan.

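### The memory test cannot be assumed unexpected at the second scan, and the 180-word list forces at least half of that visit's words to repeat

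*Protocol article*

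**What the plan says.** Under Functional MRI (fMRI) datasets, the article takes from a published source of 555 rated trait words "a list of 90 unambiguously positive and 90 unambiguously negative words". The encoding phase is specified as follows: "During the encoding task, 60 personality trait words, half of which are unambiguously positive, will be presented each for 500 ms". Participants do this categorisation first "and then an unanticipated incidental memory (retrieval) task". The retrieval phase shows 120 words: the 60 already categorised, plus 60 new ones split equally by valence. Participants judge each word as old or new.

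The Follow-up assessment section says of the second visit: "All participants will complete the same fMRI tasks collected during the first MRI visit". It names encoding and retrieval among those tasks. CBT patients return about 24 weeks after their first therapy appointment, and controls at least 24 weeks after their first scan. The article mentions no second word list and no allocation of words to visits.

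The Longitudinal data analysis plan fits a 2 × 2 group × time model to the activation data and attributes a significant interaction to CBT. The Discussion gives one reason for scanning controls twice: to keep adolescent development from being mistaken for treatment change. It does not mention familiarity with the tasks.

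**The concern.** The task is defined by participants not knowing that a memory test will follow. Everyone who returns has taken that test before. If some remember it, they may try to memorise words at the second encoding phase, and encoding is then no longer purely incidental. The stated list is also too short for a complete second set of words, so the stimuli at the two visits differ in prior exposure as well.

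What is at stake is how this task's group × time interaction is read. The two groups are not randomised against each other: one is moderately to severely depressed at the first scan and the other is healthy. Nothing guarantees that anticipating the test, or meeting words again, changes activation equally in both. Any inequality would appear in the interaction that the plan attributes to CBT.

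The article treats comparable exposure effects as relevant elsewhere. It bars overlap between the go/no-go words and the words of this task, and it varies the order of the faces to limit habituation. It states no equivalent safeguard across visits.

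**Working it through.** **Inputs** (all from Functional MRI (fMRI) datasets unless noted): list of 90 positive + 90 negative words; 60 words at encoding, half positive; 120 at retrieval, of which 60 old and 60 new; 384 volumes; TR 2 s; same task at visit 2 (Follow-up assessment).

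**1. The article's own figure.** Run length = 384 × 2 s = 768 s = 12.8 min, which agrees with the stated 13 minutes or so. If retrieval is timed like encoding (0.5 s fixation + 0.5 s word + 3 s mean interval = 4 s; an assumption, since the article gives no retrieval timing), then 60 + 120 = 180 presentations take 180 × 4 = 720 s = 12.0 min. One run therefore plausibly holds both phases, and the word counts apply to each visit.

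**2. Distinct words per visit.** 60 encoded + 60 new = 120 (60 per valence). A list of 180 (90 per valence) is enough for one visit.

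**3. Two visits.**
- Needed without overlap: 2 × 120 = 240 (120 per valence).
- Available: 180 (90 per valence).
- Shortfall: 240 − 180 = 60 (30 per valence).
- Unused after visit 1: 180 − 120 = 60.
- Least number repeated at visit 2: 120 − 60 = 60, and 60/120 = 50%.

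This is a floor. If the same task means the same words, all 120 repeat.

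**4. Where the 60 unused words go decides what repeats.**

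| Unused words used as | Visit-2 encoded words seen at visit 1 | Visit-2 distractors seen at visit 1 |
|---|---|---|
| encoded words | 0 of 60 | 60 of 60 |
| distractors | 60 of 60 | 0 of 60 |
| even split | 30 of 60 | 30 of 60 |

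Only in the second row is every word scored as new truly unseen. No row reproduces visit 1, where no word in either category had been shown at an earlier visit.

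**5. What reaches the interaction.** Write the change in patients as C + D + Rp and in controls as D + Rc. C is the CBT effect, D is development (taken as equal in both groups), and Rp and Rc are the effects of repeating the task. The interaction is

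(C + D + Rp) − (D + Rc) = C + (Rp − Rc).

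If Rp = Rc, repetition drops out. If not, the difference is added to C and cannot be told apart from it. The documents give no value for Rp or Rc, so the bias cannot be sized.

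**The case against.** The strongest case on the other side has four parts.

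- **Memory of the first visit is unknown.** A reader might infer that every returning participant expects the test and that the two scans measure different processes. The documents do not support this. Each encoding word is shown for 500 ms, the gap is about 24 weeks, and nothing says what adolescents remember of the words or of the surprise. Retrieval is an explicit old/new judgement at both visits, so lost surprise bears mainly on encoding. This stands.
- **The old/new judgement need not be corrupted.** A reader might infer that repeats make the response invalid. The 60 unused words are exactly enough to serve as all the visit-2 distractors, and every new word is then truly unseen. The judgement is literally false only where a previously shown word serves as a distractor. This stands too. Allocation by visit is also detail that an article may leave to a fuller document, but no allocation can remove the 60-word shortfall.
- **Controls repeat the task.** Whatever repetition does equally in both groups falls into the main effect of time. This is correct and removes the common part. It leaves Rp − Rc, and equality there is an assumption the article does not discuss. The waiting time is also anchored to different events in the two groups.
- **The first visit is not shown to be compromised.** A reader might infer from "three similar tasks brief in length will be practiced on a computer in advance of the actual scan" that practice gives the recognition test away. The article does not say that practice includes recognition, so the inference fails.

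A reader might also conclude that the task should leave the longitudinal analysis. That is out of proportion to a differential effect nobody has quantified.

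**Conclusion.** The point holds as a minor one. On the article's own numbers, the list is 60 words short of two full sets, so at least 60 of the 120 visit-2 words (50%) repeat. This assumes that the 180-word list is the only source of words and that visit 2 uses the same counts as visit 1. Separately, the incidental premise cannot be assured at visit 2. That is a limit on what may be claimed, and does not show that the premise fails.

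The consequence is confined to the group × time contrast for this one task, chiefly its encoding phase. Bias arises only if test expectation or word re-exposure acts differently in patients and controls. That is plausible, but its size is unknown. The baseline case-control comparison, the baseline predictors of response and the other fMRI datasets are untouched. So is the power calculation for CBT-related change, which rests on amygdala response in a facial emotion task.

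**What to change.** 1. Draw two non-overlapping sets of 120 words (240 in all, 120 per valence) from the 555-word source, and counterbalance which set comes first within each group. With the planned 40 CBT patients and 40 controls, that is 20 per order in each group. Counterbalancing keeps word set from being confounded with visit. This assumes that the source yields 120 unambiguous words per valence, which cannot be checked from the article.
2. If it does not, reserve the 60 words unused at visit 1 as the visit-2 distractors, so that a word scored as new has not been shown before. State that the encoded words are then repeats.
3. Keep the task in the longitudinal analysis. Describe memory at visit 2 as possibly anticipated, since new words do not restore surprise. Label this task's group × time contrast exploratory, and do not present it as identifying the effect of CBT.

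The cost is stimulus-list work, a few sentences in the plan, and one contrast with a weaker claim attached.

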### Follow-up assessment

Patients who were randomized to the CBT arm of the IMPACT clinical trial who have completed a minimum of 6 out of a maximum of 20 offered CBT therapy sessions will be invited back for a second MRI visit approximately 24 weeks following their first therapy appointment. All healthy comparison participants will be invited back for a second MRI visit at least 24 weeks from their first scan date to ensure a comparable length of time has passed between scans across groups. Due to financial constraints, no sMRI and DTI sequences will be performed at the second MRI visit. All participants will complete the same fMRI tasks collected during the first MRI visit (e.g., implicit facial expression recognition, emotional go/no go, encoding and retrieval, and resting state tasks). In line with procedures undertaken at the first scan, STAI measures will be obtained prior to scanning whereas SMFQ and Bond VAS measures will be obtained after the scan.

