### Aims

Neuroimaging examinations of adolescents with MDD provide an opportunity to reveal and differentiate pathophysiological and therapeutic neural structure and function between first episode sporadic as well as at risk recurrent forms of this disorder. Using a repeated-measures design in selected cases that have completed psychological treatment provides a longitudinal neuroimaging investigation of therapeutic effects that have the added potential of revealing neural sites that constitute state or trait markers of illness and treatment insensitivity.

MR-IMPACT will therefore examine neural markers of moderate to severe unipolar depression in adolescence and neurobiological predictors of recovery from depression. Specific objectives of MR-IMPACT are as follows:

• To define the profile of brain structural and functional differences in adolescent patients with depression at baseline compared to a group of healthy adolescent participants.

• To assess baseline measurements of brain structure, functional activation and connectivity, focusing on neural systems implicated in adult MDD (ACC and other fronto-limbic components) as predictors of symptomatic response to each of the three types of psychological treatments in the short-to-medium term (up to 86 weeks after the start of treatment).

• To measure changes in brain functional activation and connectivity before and after a course of CBT and development-related changes in brain function measured in a comparison group of healthy participants to permit identification of treatment-related changes in brain function.

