### Sample size and power calculations

To effectively test the presence of a relationship between pre-treatment imaging markers and post-treatment symptomatic response the study sample size will need to be large enough to overcome the neuroimaging problem of multiple comparisons across the ~300,000 intra-cerebral image voxels and also account for participant attrition. The attrition rate observed during a similar trial (i.e., Adolescent Depression Antidepressants and Psychotherapy Trial [ADAPT]) with a 28-week follow-up period was just 2% [43]. Allowing for an even greater attrition rate of 20% on a pre-treatment sample size of 40 patients per treatment arm, it follows that 32 patients will be available for post-treatment scans. Assuming an effect size of the same size as that observed in a previous study of adults with MDD (R ≥ 0.76 for grey matter volume [GMV] and symptom response in ACC) [8] and a conservative two-tailed probability of p <0.001 to control for multiple comparisons in a whole brain analysis of imaging data, and at least 32 patients completing post-treatment scans, the power to detect a true effect will be at least 95%. Thus with pre-treatment imaging data from 40 patients per treatment arm, the study is strongly powered to assess imaging predictors of recovery following treatment for MDD.

To detect CBT-related changes in brain function, a previous fMRI study of adult MDD [9] and a pilot study examining components of variance in a facial emotion perception task [44] are used to inform calculations of statistical power. Activation of the left amygdala by facial emotion processing showed an effect of antidepressant treatment of d = 1.02 [9]. A similar effect size of CBT will be assumed for the current study, with empirical estimates of between-subject and between-session variance in amygdala response [44] suggesting that a minimum power of 80% will be needed for detection of a true treatment effect. Considered together with a false positive rate of 5%, a minimum of 30 participants will be needed for the detection of CBT-related changes in brain function. The effects obtained in 40 patients in the CBT arm, compared to 40 healthy adolescents, should therefore be sufficiently powerful in size to detect therapeutic changes in amygdala activation equivalent to that observed from antidepressant medication treatment studies of adult patients with MDD.

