#### *Longitudinal data analysis plan*

For the fMRI datasets collected at baseline and 24 weeks, we will fit a balanced, mixed effects 2 × 2 (group × time) analysis of variance (ANOVA) model to the brain activation data acquired on patients treated with CBT and healthy adolescents. A significant group × time interaction will identify the effect of CBT, for which appropriate post-hoc tests will be performed. Nonparametric statistical methods of inference correcting for multiple comparisons will be applied to statistically evaluate the main effects of group and time point, and any group × time interaction [50-52].

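### The CBT change analysis is sized on 40 patients although 32 or fewer are expected to have two scans, and its interaction describes change among attenders only

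*Protocol article*

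**What the plan says.** Three sections of the protocol article fix the CBT change analysis.

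- **Follow-up assessment.** The CBT patients to be rescanned are those "who have completed a minimum of 6 out of a maximum of 20 offered CBT therapy sessions will be invited back". For controls there is no comparable condition: "All healthy comparison participants will be invited back for a second MRI visit at least 24 weeks from their first scan date".
- **Longitudinal data analysis plan.** For the two sets of scans, "we will fit a balanced, mixed effects 2 × 2 (group × time) analysis of variance (ANOVA) model". The reading of the result is stated in advance: "A significant group × time interaction will identify the effect of CBT".
- **Sample size and power calculations.** The first paragraph allows 20% attrition on 40 patients per arm and arrives at 32 for scans after treatment. The second paragraph, on CBT-related change, borrows an effect from an adult study that "showed an effect of antidepressant treatment of d = 1.02". It gives a minimum of 30 participants at 80% power and a 5% false positive rate, and then relies on "The effects obtained in 40 patients in the CBT arm, compared to 40 healthy adolescents".

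The Aims describe the rescanned group as "selected cases that have completed psychological treatment". The Discussion repeats the six-session condition, but its limitations paragraph does not mention selection by attendance.

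**The concern.** The change analysis is the one analysis in the study that needs two scans per person. Its power statement nevertheless uses the number with a first scan. The attrition allowance made one paragraph earlier is not carried over, and the session rule is not reflected at all. The stated model presumes equal groups with both scans, which the article's own figures make unlikely.

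The second issue is interpretation. Attendance is decided after allocation and may depend on engagement, severity or early response. Patients who leave before six sessions contribute no second scan, yet the interaction is to be read as the effect of CBT without restriction. What is at stake is the group to which the finding applies. This matters because the study is described as pragmatic, and its eligibility criteria are kept broad so that the sample represents routine clinic cases.

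**Working it through.** **Inputs from the article.** 40 patients per arm; 40 controls; 20% attrition allowance; 2% attrition seen in a similar trial; d = 1.02; 80% power; 5% alpha; stated minimum 30; at least 6 of up to 20 sessions.

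**Assumptions.** The test is two-sided, and d is read as a between-group difference in change in units of the SD of change. The pilot variance components are not given, so the authors' exact calculation cannot be rebuilt. All power figures below are for a single test at 5%, as in the article's own calculation.

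**1. Reproduce the stated minimum of 30.** n per group = 2(1.960 + 0.842)² / 1.02² = 15.1, or about 30 in total (16 per group, 32 in total, when rounded up). By normal approximation, 15 per group gives 79.8% power. Read as 30 per group, power would be 97.7%, far from the stated 80%. The figure therefore reproduces only as a total over two groups, although the article does not say which is meant.

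**2. CBT patients with two scans.** 40 × (1 − 0.20) = 32. At 2% attrition, 40 × 0.98 = 39. Both are below 40 before the session rule is applied.

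**3. Effect on power.** The two-sample t test has non-centrality d√(n₁n₂/(n₁+n₂)). For 40 v 40 this is 1.02 × √20 = 4.56 and power is 99.5%. For 32 v 32 it is 1.02 × √16 = 4.08 and power is 98.0%. The share of the 32 reaching six sessions is not given, so a range is assumed:

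| Share with ≥6 sessions (assumed) | CBT patients | Power v 32 controls | Power, controls cut to match |
|---|---|---|---|
| 100% | 32 | 98.0% | 98.0% |
| 90% | 28 | 97.2% | 96.3% |
| 80% | 25 | 96.4% | 94.2% |
| 70% | 22 | 95.1% | 91.1% |
| 60% | 19 | 93.2% | 86.4% |
| 50% | 16 | 90.3% | 79.7% |

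Forcing balance discards controls and costs power in every row below the first. At a smaller effect, d = 0.7 (an assumption), power is 87% at 40 v 40, 79% at 32 v 32 and 73% at 25 v 32.

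**4. Selection.** If a proportion p qualifies and the tendency to attend correlates ρ with neural change, mean change among attenders shifts by ρφ(z)/p SD, where z is the normal quantile of p. With |ρ| = 0.3, p = 0.8 gives 0.3 × 0.280/0.8 = 0.105, and p = 0.6 gives 0.3 × 0.386/0.6 = 0.193. Both ρ and p are assumed. The sign is open: disengaged non-responders leaving would inflate the change, and early improvers leaving would shrink it. This shows the possible scale and is not an estimate.

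**5. Wording.** Six of 20 is 30% of the maximum offered. The rule sets a minimum exposure, which fits poorly with the Aims' description of completed treatment.

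**The case against.** The strongest reply is that the attendance condition is deliberate and disclosed. The objective is change before and after a course of CBT, which is a mechanistic question. The comparison is with healthy adolescents, so no randomised contrast is broken, and controls have no sessions to attend. This stands: conditioning on exposure is defensible. It does not support an unqualified reading of the interaction as the effect of CBT.

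A reader might infer that the analysis is underpowered or falls below its minimum. That would need 30 to be a per-group figure, in which case losing three of the 32 to the session rule would leave 29. The figure reproduces only as a two-group total, and power stays high at d = 1.02. The gap between 30 and 40 could also be an unstated margin. What remains is an inconsistency between 40 and 32.

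A reader might also infer that the CBT effect is overstated by a known amount. The article gives neither the qualifying share nor the correlation, and the sign could reverse.

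On the model, balanced may simply describe the planned layout. The article already calls the model mixed effects and does not say that incomplete pairs are dropped. Handling of missing scans may sit in an analysis plan not shown here. That is fair, but the stated layout still conflicts with the attrition the article expects.

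Finally, 20 is a ceiling on sessions offered, so the 30% figure alone does not show that treatment was incomplete.

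**Conclusion.** The point holds in limited form. The number counted for the two-scan analysis (40) contradicts the article's own expectation (32, before a session rule that can only reduce it), and a balanced layout is not what those figures predict. The interaction describes change among patients who attended at least six sessions. Any selection bias relative to the whole CBT arm is of unknown size and direction.

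The effect on power is small at the assumed d = 1.02: 99.5% falls to 98.0% at 32 v 32, and power is still about 80% at 16 v 16. This rests on a two-sided 5% test, on d applying to the between-group difference in change, and on the article's 20% attrition. It would matter more if the true effect were smaller. The consequence lies mainly in the analysis model and in what may be concluded.

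**What to change.** - **Sample size and power calculations:** replace 40 CBT patients with the number expected to have two scans after attrition and the session rule (32 or fewer), and state whether 30 is a total or per group.
- **Longitudinal data analysis plan:** replace the balanced ANOVA with a linear mixed model that allows unequal groups and keeps every baseline scan. Such a model extends to patients not rescanned only under a missing-at-random assumption, so show the estimate from patients with both scans beside it.
- **Same section:** compare rescanned and non-rescanned CBT patients on baseline features, and state the conclusion as change among patients attending at least six sessions.
- **Aims and Follow-up assessment:** reconcile the description of completed treatment with the 6-of-20 rule.
- **Discussion:** list attendance selection among the limitations.

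The cost is some extra analysis work and a narrower conclusion. Inviting every CBT patient with a baseline scan, with sessions attended as a covariate, would address selection more directly but is optional. At an assumed 60–80% qualifying it means 8 to 16 more invitations out of 40, and the article reports that budget limits already removed sequences from the second visit.
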